### Participants

All NYS Office of Mental Health (OMH) child-serving public outpatient mental health clinics across the five boroughs of New York City (NYC) are eligible to participate. To secure the sample of clinics, the study team obtained a master list of 168 clinics from OMH. Based on prior statewide studies conducted by the investigative team, it was estimated that approximately 80% of the clinics would participate; thus, we estimated that approximately 134 clinics will enroll in the study.

At each clinic, we anticipate enrolling 20 caregiver/child dyads (a minimum of *n* = 896 per arm, or 2688 total), and two providers per arm, yielding a total of 268 providers. Researchers will consecutively consent families to participate in the study until a sample of 20 caregiver/child dyads per clinic is achieved. Eligible caregivers are 18 years of age or older, English or Spanish speaking, and the primary caregiver of a 7- to 11-year-old child with ODD. Eligible providers are staff members who work in a participating clinic in a clinical capacity, and are English speaking.

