### Clinic involvement

Of the approximately 134 clinics that will be invited to participate; 37 clinics have been enrolled in the study thus far. Data collection has begun at 14 clinics in the SAU clinic, eight clinics in condition 1 and seven clinics in condition 2. Others have agreed to participate and data collection will begin shortly.

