### Trial status

Clinic recruitment for standard care has been completed. Data collection has been initiated, and one third (*n* = 792) of the sample of providers and caregivers have been enrolled. Clinic recruitment for MFG and MFG + CIT have been initiated, and some clinics have already completed training and have participated in adaptation meetings. Recruitment of clinics for the experimental arms will be ongoing until enrollment targets are met. Groups for both MFG and MFG + CIT are expected to begin in the first trimester of 2017. A populated Standard Protocol Items: Recommendations for Interventional Trials (SPIRIT) Checklist (see Additional file 1) and Figure ( see Fig. 3) for all study protocols are included as an additional file (see Additional file 1 and Fig. 3). A composition of the data monitoring commitee has also been included (see Additional file 2).

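### The figure of 896 dyads per arm is an expected count, not a minimum, and the article's own enrolment figures do not support it for the standard-care arm

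*Protocol article*

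**What the plan says.** All places are in the protocol article.

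- **Participants.** On the clinic list, "the study team obtained a master list of 168 clinics from OMH". From earlier statewide studies, "it was estimated that approximately 80% of the clinics would participate", and so "we estimated that approximately 134 clinics will enroll in the study". Each clinic is to contribute 20 dyads, and consecutive consenting ends when a clinic reaches 20. The resulting sample is called a minimum of "896 per arm, or 2688 total", with 268 providers.
- **Abstract, Methods/design.** All New York City public outpatient clinics have already been invited; the expected participation is 134 clinics, 268 providers and 2688 dyads.
- **Clinic involvement.** The same number appears as an invitation count: "Of the approximately 134 clinics that will be invited to participate". Of these, 37 are already enrolled. On progress by arm: "Data collection has begun at 14 clinics in the SAU clinic, eight clinics in condition 1 and seven clinics in condition 2". Further clinics are reported as willing and about to start.
- **Trial status.** "Clinic recruitment for standard care has been completed". Recruitment of clinics continues for the two experimental arms until their targets are met. One third, given as 792, "of the sample of providers and caregivers have been enrolled".

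**The concern.** These statements do not fit together. A per-arm minimum should be a number that every arm will at least reach. Here one arm is closed to new clinics, each clinic has a cap of 20 dyads, and the enrolled clinics reported for all three arms together are fewer than that one arm would need.

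The arm in question is the comparator. Hypothesis 1 of Aim 1 sets the family-group intervention against standard care on child behaviour and functioning, which are the primary outcomes. Continued recruitment in the experimental arms cannot make up for a small standard-care arm. A reader who takes 896 per arm at face value would therefore credit that comparison with more information than the reported enrolment supports.

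**Working it through.** **Step 1. Reproduce the stated figure (inputs from Participants).**

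- Clinics: 168 x 0.80 = 134.4
- Dyads: 134.4 x 20 = 2688
- Per arm: 2688 / 3 = 896
- Providers: 134 x 2 = 268, i.e. two per clinic

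Both 896 and 2688 follow exactly. They are feasibility counts; no power formula is involved. With whole clinics, 134 x 20 = 2680, or 893 per arm, a rounding difference of 8 dyads.

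**Step 2. Is it a minimum?**

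Because 20 is the stopping point, clinics x 20 is a ceiling.

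- Clinics needed for 896: 896 / 20 = 44.8, so 45
- Clinics needed for three such arms: 3 x 45 = 135, one more than the 134 expected

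The figure is what results if 80% of clinics join and each fills its quota. It is not a floor.

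**Step 3. What can standard care supply?**

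Inputs are 37 clinics enrolled and 14 / 8 / 7 with data collection begun (Clinic involvement), and standard-care clinic recruitment completed (Trial status). Both sections are assumed to describe the same date.

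| Standard-care clinics | Dyads at 20 each | Share of 896 |
|---|---|---|
| 14 (data collection begun) | 280 | 31% |
| 37 - 8 - 7 = 22 (all remaining enrolled clinics) | 440 | 49% |
| 37 (all enrolled clinics; excluded, since 15 are experimental) | 740 | 83% |
| 45 (needed) | 900 | 100% |

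Reaching 45 would take 45 - 22 = 23 standard-care clinics beyond the most that the reported counts allow.

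**Step 4. The number 134.**

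The Abstract and Participants give 134 as clinics expected to enrol; Clinic involvement gives it as clinics to be invited. At 80% uptake, enrolling 134.4 requires inviting 134.4 / 0.80 = 168. If only 134 were invited, even full uptake would give 134 x 20 = 2680.

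**Step 5. The number 792.**

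- Against dyads: 792 / 2688 = 29.5%
- Against dyads plus providers: 2688 + 268 = 2956; 792 / 2956 = 26.8%; one third would be 985
- Total implied if 792 is one third: 792 x 3 = 2376, which the article states nowhere

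**Step 6. Illustration of precision only.**

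The article gives no power, effect size or intracluster correlation (ICC). Assume a two-sided 5% test, 80% power, 20 dyads per clinic and an ICC of 0.05. The design effect is then 1 + 19 x 0.05 = 1.95, and the detectable difference in SD units is 2.80 x sqrt(1.95 x (1/n1 + 1/n2)).

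- 896 v 896: 0.185
- 440 v 896: 0.228
- 280 v 896: 0.268

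For an ICC between 0.02 and 0.10, the first line runs from 0.155 to 0.225 and the last from 0.225 to 0.327. The 896 in the other arm is itself an assumption.

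**The case against.** The strongest defence is that the sample size was calculated correctly and the rest is loose wording in a progress report. Much of this stands.

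- **The calculation.** A reader might infer that 2688 is miscalculated because 134 x 20 = 2680. It is not: the unrounded product gives 2688 exactly, and the text calls 134 approximate.
- **The invited count.** A reader might apply the 80% again to 134 and conclude that the real target is 107 clinics and 2144 dyads. No section states such a target. Two places give 134 as enrolling, so the word invited is most simply a slip. It still needs correcting.
- **The shortfall.** A reader might infer that standard care falls short however the article is read. That goes too far. Clinic involvement reports counts to date and mentions others who have agreed. If it was written before Trial status, or if those others lie outside the 37, the final standard-care count is unknown.
- **The 792.** A reader might hold that 792 is impossible because the 29 clinics collecting data can contain only 29 x 22 = 638 caregivers and providers. But 792 counts people enrolled, and 37 enrolled clinics could hold 37 x 22 = 814. A reader might also take 792 as the complete standard-care arm (36 clinics, 720 dyads); the article never assigns it to one arm.
- **Power.** A reader might infer that the trial is underpowered. The article makes no power claim that these counts could contradict.

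The defence does not explain the label minimum, the absence of any figure that supports 45 standard-care clinics, the double use of 134, or a third that is not a third.

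**Conclusion.** The point holds as a fault of internal consistency, not of multiplication. Three things are wrong as written:

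- The per-arm size is labelled a minimum although it is an expectation under a cap.
- No count in the article supports that size for standard care, the one arm whose clinic recruitment is declared complete.
- The 134 and the 792 are each used in a way that conflicts with the sample described under Participants.

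The range of 280 to 440 depends on the two status sections sharing a date and on the 37 being all clinics enrolled by then. Without that assumption the size of the standard-care arm is undetermined, but it remains unsupported. The conflict over 134 and the mismatch of 792 with one third do not depend on it. The detectable differences show only how much the size of this arm could matter; they rest on an assumed ICC and do not show that a planned power has been missed.

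**What to change.** 1. Give one set of clinic counts, by arm where applicable and with a date: listed, invited, agreed, enrolled, data collection begun. Settle whether 134 is the number invited or the number expected to enrol.
2. State the final number of standard-care clinics and the dyads they can supply at up to 20 each. Replace the minimum of 896 per arm, and the total, with the supported sizes, unequal if need be. Where a number is a projection, call it expected.
3. Say whom the 792 counts (caregivers, providers or both, and in which arms). Then either correct the fraction or state the total of which it is one third.

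This is a change of text only. It asks for no further enrolment and leaves the design and analysis alone. The one drawback for the authors is that the stated size may look less favourable.

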### Sampling procedure

A multi-stage sampling procedure was undertaken, with randomization occurring at the agency level in order to prevent an unbalanced representation of clinics across the treatment arms and to conduct a sub-study in which we will examine the impact of clinic choice upon outcomes. From a master list of OMH-licensed agencies and corresponding clinics within the five boroughs of NYC that was received from The Office of Mental Health in 2016, the investigative team created three lists: (1) single-site (agencies that had only one outpatient mental health clinic, (2) multi-site agencies with between two to four clinics and, (3) mega-agencies that had five or more clinics. Each list was organized alphabetically.

A separate randomization process was employed for each list. Clinics within single-site agencies were stratified by borough, and a random number generator was employed to randomly assign clinics to one of three conditions: (1) condition 0, which was services as usual (SAU), (2) condition 1, the 4Rs and 2Ss MFG, and (3) condition 2, the 4Rs and 2Ss MFG + CIT (all three conditions are described more thoroughly on page 8). Once the initial number was generated, subsequent clinics were assigned the next number in the sequence (e.g., if the first clinic received condition 0, the next clinic would be enrolled in condition 1, and so forth). Of note, the research staff member was unaware what numbers corresponded with which condition (e.g., that a clinic in condition 0 would be randomized to SAU). This procedure was undertaken in order to minimize allocation bias.

Multi-site agencies with between two and four clinics were also organized alphabetically within borough, and a random number generator was used to assign the initial clinic to a particular condition. Moreover, additional clinics that were part of the agency in which the initial clinic was randomized received the same condition. For example, if one clinic was assigned condition 0, the remaining clinics, regardless of which borough they were located in, were also assigned to condition 0.

Finally, agencies with five or more clinics were given the choice to select the study condition in which they would participate with an even distribution of these mega agencies occurring across the three study conditions.

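### Single-site clinics are allocated by fixed rotation after a random start, and masking the code labels does not conceal condition while clinics are being recruited

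*Protocol article*

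**What the plan says.** The Sampling procedure section of the Protocol article divides agencies into three lists by number of clinics. Of these lists it says: "Each list was organized alphabetically". Each list is then handled differently.

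- **Single-site agencies.** "Clinics within single-site agencies were stratified by borough, and a random number generator was employed to randomly assign clinics to one of three conditions". The mechanism follows: "Once the initial number was generated, subsequent clinics were assigned the next number in the sequence", with the example that "if the first clinic received condition 0, the next clinic would be enrolled in condition 1, and so forth".
- **Multi-site agencies (two to four clinics).** A random number sets the condition of the initial clinic, and the agency's other clinics take the same condition. No rotation is described.
- **Mega-agencies (five or more clinics).** These chose their condition and were not randomised.

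The safeguard offered in the single-site paragraph is that "the research staff member was unaware what numbers corresponded with which condition". The paragraph closes: "This procedure was undertaken in order to minimize allocation bias".

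Two other sections bear on the point. Participants gives a master list of 168 clinics, of which about 80% were expected to take part. Trial status reports that clinic recruitment for standard care is finished, while recruitment for the two experimental arms has started and will run until targets are reached.

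**The concern.** Two things are presented as stronger than they are.

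The first is the word random. A generator supplies one number and every later single-site clinic in that run follows by rotation. The clinics are not randomised one by one, and they are not randomised in blocks.

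The second is the protection against allocation bias. Not knowing what 0, 1 and 2 stand for prevents the person who applies the numbers from favouring a condition. Concealment is a different property: those who approach a clinic, and the clinic itself, should not know its condition until it has agreed to join. Masked labels do not provide that. Rotation weakens it further, because one disclosed condition reveals its neighbours on an alphabetical list.

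At stake is the comparability of the clinics that end up in each arm. The arms ask very different things of a clinic: usual services; training plus supervision; or both of these plus implementation-team meetings. If condition is known before agreement, willingness to join, or the effort spent on recruiting a clinic, can depend on it. Researchers later enrol families within those clinics, so the same knowledge is present there too.

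**Working it through.** **Inputs from the Protocol article.** Three conditions, a random first number, then rotation in alphabetical order (Sampling procedure); five boroughs, 168 listed clinics, about 80% expected to participate (Participants). The article does not give the number of single-site clinics or the number per borough, so run length k is an assumption below.

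**The plan's own figures.** 168 × 0.80 = 134.4, which matches the stated 134 clinics. 134.4 × 20 = 2688 dyads, and 896 × 3 = 2688. These reproduce. No figure in the article is tied to the allocation method, and nothing here changes the sample size.

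**Expected non-participation.** 168 − 134 = 34 clinics, about 20% of the list.

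**Possible allocations in one run.**

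| Random start | Sequence down the list |
|---|---|
| 0 | 0, 1, 2, 0, 1, 2, … |
| 1 | 1, 2, 0, 1, 2, 0, … |
| 2 | 2, 0, 1, 2, 0, 1, … |

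At any position each code appears once across the three starts, so each clinic's chance of each arm is 1/3. Jointly there are only 3 allocations. The statement that "Clinics within single-site agencies were stratified by borough" suggests a separate start in each borough but does not say so outright:

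- one start for the whole single-site list: 3 allocations
- one start in each of five boroughs: 3^5 = 243 allocations

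In a re-randomisation test confined to single-site clinics, the smallest attainable p-value would be 1/3 = 0.33 or 1/243 = 0.004. This shows how little randomness the scheme contains; the article does not plan such a test.

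**Predictability.** Suppose an observer knows the rotation order, guesses the first clinic in a run with probability 1/3, and then learns its condition. The remaining k − 1 clinics follow with certainty, so the expected share guessed correctly is (1/3 + k − 1)/k.

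| Assumed k | Rotation | Independent draw per clinic |
|---|---|---|
| 3 | 78% | 33% |
| 6 | 89% | 33% |
| 12 | 94% | 33% |
| 18 | 96% | 33% |

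Balanced designs also lose some unpredictability. With permuted blocks of three and known block boundaries, the share is (1/3 + 1/2 + 1)/3 = 61%. Rotation exceeds this at every k shown.

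**Was condition known before clinics joined?** Sampling procedure masks one staff member to the code meaning at assignment. Trial status has one arm closed to clinic recruitment and two still open. Recruitment can be closed for one arm only if those running it know which listed clinics belong to that arm. Together the two sections indicate that condition was known on the recruiting side before clinics agreed. They do not say when the clinics themselves were told.

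**The case against.** The strongest defence is that predictability does most harm when a recruiter can choose which unit to enter next. Here the units came from an outside master list in alphabetical order, and the person assigning numbers did not know what they meant. That does limit steering at assignment, so it would be wrong to say the safeguard achieves nothing.

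A second defence also carries weight. Refusal that depends on condition arises from when the condition is disclosed, and a properly randomised list drawn in full beforehand would be exposed in the same way. Rotation adds one thing: the conditions of clinics not yet approached can be worked out without access to the list. Timing of disclosure is therefore the main practical lever.

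A reader might infer more than the document supports in four ways:

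- **That all lists were rotated.** Rotation is stated for single-site clinics only. Multi-site agencies may have had one draw each, and mega-agencies were not randomised.
- **That selection has been shown.** The article reports that "Data collection has begun at 14 clinics in the SAU clinic, eight clinics in condition 1 and seven clinics in condition 2". Recruitment for standard care finished first, which explains the higher count in that arm. The counts may also include mega-agencies that chose their arm. They are not evidence of bias.
- **That borough and agency-size list are left out of the model.** The Analytic strategy section does not mention them, but a condensed article may leave covariates to the full protocol or analysis plan. Silence here is not an error.
- **That few possible allocations means a biased estimate.** It does not. The marginal chances are equal, and the count describes how much randomness there is.

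**Conclusion.** The point holds for the single-site list. The procedure is systematic allocation with a random start: 3 possible allocations per run, or 243 in all if each of the five boroughs had its own start. Under the assumed run lengths of 3 to 18 clinics, 78% to 96% of assignments could be deduced, against 33% with independent draws. Masking the code labels gives partial protection at assignment and none during clinic recruitment.

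The conclusion that recruiters knew the condition is an inference from arm-by-arm recruitment in Trial status. With about 20% of listed clinics expected not to join, there is room for differential uptake. Neither its presence nor its direction or size can be established from the article.

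This does not invalidate the trial. It is a misdescription that should be corrected, together with an exposure to selection that can still be reduced, because recruitment to the experimental arms is open, and can be examined across all arms.

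**What to change.** 1. **Describe the method as it was done.** Call the single-site procedure systematic allocation with a random start, state whether there was one start per borough or one overall, and do not present code masking as allocation concealment. Cost: wording.
2. **Disclose after agreement.** For randomised clinics not yet approached, keep the existing assignment but reveal it only once the clinic, or the agency where clinics share a condition, has agreed to join. The downside is that some will withdraw after disclosure; count and report these by assigned arm. Redrawing the remaining clinics is not advised, since it would mix two allocation mechanisms within an arm and, if done clinic by clinic, would break the rule that an agency's clinics share one condition.
3. **Adjust for what was used in allocation.** Include borough and agency-size list (single-site or multi-site) in the arm comparisons, and keep the self-selected mega-agencies separate from the randomised comparison. With five boroughs and two randomised lists this takes 4 + 1 = 5 clinic-level parameters. If the full analysis plan already does this, a sentence confirming it is enough.
4. **Check for differential uptake.** Tabulate enrolled against non-enrolled clinics by assigned arm, using the state mental health office data described under Organizational characteristics. This assumes those datasets cover clinics that did not enrol. Cost: one table.

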### Description of the conditions

The study consists of three arms: two active treatment and one comparison condition:The 4Rs and 2Ss Multiple Family Group interventionThe 4Rs and 2Ss MFG is a 16-week group for urban children of between 7 and 11 years of age with ODD and their caregiver(s). In this model, six to eight families meet in weekly sessions focused on addressing family and parenting factors associated with behavior problems [30–33]. Session content also addresses lack of social support and high stress, which are two factors known to hinder treatment attendance [34–36]. Families are provided with free childcare, transportation expenses, and a meal to address common logistical barriers to attendance [8]. Moreover, perceptual barriers, such as stigma and fears of being blamed for their child’s difficulties, are targeted through group processes which normalize family difficulties, validate their expertise in solving problems, and promote mutual aid [37]. Providers who participate in this condition will attend a 5-h training to learn the 4Rs and 2Ss MFG model; thereafter, they will participate in bimonthly supervision over the course of implementationThe 4Rs and 2Ss MFG + CITIn addition to implementing the model and receiving supervision, a CIT consisting of providers, a clinic director and supervisor will participate in ongoing meetings with the research team’s adaptation specialist for a guided analysis of the structure, content and processes of the treatment model, including those that are amenable to modification and those that must remain unchanged in order to maintain fidelityStandard careStandard care includes the services that the clinic normally provides to children with behavioral problems, including outpatient mental health therapy and pharmacology

